#### Intervention - the China Monitoring (CHMON) feedback system

The CHMON system utilized for the project is a ZGPAX S8 [13]. The S8 is a full android Smart watch encapsulated in a wrist-wearable unit. As such it is capable of running apps written for it and operating in a stand-alone manner. The hardware specifications for the ZGPAX S8 are shown in Table 1.

**Table 1 Tab1:** Hardware specifications for the ZGPAX S8 android Smart watch

	Hardware specification
Size	58 × 42.5 × 13 mm
Weight	67 g
Screen	40 mm capacitive touchscreen
Battery	3.7 V/470mAh Li-ion (rechargeable)
CPU	MTK6572 Dual Core 1.2 GHz
Memory	12 GB total
RAM	512 MB
Android version	4.4.2
Sensors	GPS, accelerometer
Connectivity	WiFi, Bluetooth, 2G, 3G
Waterproof	No

*CPU* central processing unit, *RAM* random access memory

The CHMON system is used both as a data gathering platform and as a feedback device to the patient in the experimental group (Fig. 2). The patient wears the device for 9 hours a day. In the intervention group, the watch will divide elapsed time into four periods of 2 hours, and one of 1 hour. In the control group the activity level is simply recorded, and no further processing occurs.

**Fig. 2 Fig2:**
[figure not shown]
The watch face: blue clock icon showing current 2-hour window and red-green bars showing activity feedback (one group only)

In the intervention group the data from the first day is used to establish baseline activity levels for each epoch. Daily activity is calculated in 2-hour periods (with one 1-hour period). Each day, the watch calculates a goal for the patient for each period, the goal being 5% higher than the activity recorded in the same period 24 hours earlier.

To gather data from the ZGPAX S8 a custom app was written, based around work by Amor et al. [14] and Ahanathapillai et al. [15], which has been used in previous work looking at physical activity monitoring, among other parameters, in older people. The app records data from the ZGPAX S8 tri-axial accelerometer and processes it to extract a measure of physical activity, the activity score [16]. A slightly modified activity score has been shown to correlate well with energy expenditure, measured in kilocalories per minute (kcal/min), in results obtained from a comparison of activity score against energy expenditure obtained from whole-room calorimetry [17].

Calculation of the activity score [16] and modification of the activity score [14] have been fully described previously; only brief details are repeated here. Raw acceleration data are recorded from the CHMON system in three orthogonal axes, X, Y and Z, at 16.6 Hz using a 30-sec on, 120-sec off interval-sampling regime. The 30-sec-on period is subsequently referred to as an epoch. Sampling was carried out in this manner to preserve battery life on the device whilst endeavoring to capture as much of the patient’s activity as possible. The intention is to compare *relative* levels of activity from day to day, over the treatment period, and between groups. It is not intended to measure actual activity. Using an accelerometer located on the wrist of the unaffected arm, and a sampling procedure covering 20% of the time should allow this without risking systematic bias.

Subsequent data processing of the raw data happens within the watch using inbuilt software in three stages. In the first stage, baseline smoothing is used to remove some of the noise from the signal that is caused by analogue to digital conversion. This has the effect of significantly reducing noise when the CHMON is stationary and where noise therefore is the overriding component in the signal. This is performed on all three axes independently.

In the second stage, the root mean squared combination of the X, Y and Z axes is calculated. The effect of gravity on the accelerometer data (causing a continuous 1 g reading towards the ground) is removed by subtracting the mean of the signal with a 3-sec sliding window. From these data, an assessment of the CHMON worn-state, either worn or not worn, is carried out, which looks to see if the data show any movement and if they do not, the CHMON system is assumed to be not worn and no further processing is applied.

In the final stage, the mean value of the data over the epoch is calculated and adjusted to increase the variance at the lower end of the value range. The value is left unrounded and is used as the activity score [12].

Activity score data from each epoch are added to a tally of activity score for the current time period and these data are used, in the feedback group only, both to provide feedback to and to set goals for the patient. Goals for a day are set to be 5% more in each period that the sum activity score obtained in the corresponding period the previous day.

There are two parts to the user interface; the clock icon and the activity tracker (Fig. 3). The clock icon shows the participant which time period they are currently in. The activity tracker shows how close the patient is to meeting their activity target for the day. All patients will see the clock icon.

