**Methods/design:**

A randomized controlled trial will be undertaken within the stroke rehabilitation wards of the Second Affiliated hospital of Anhui University of Traditional Chinese Medicine, Hefei, China. The study participants will be stroke survivors who meet inclusion criteria for the study, primarily: able to participate, no more than 4 months after stroke and walking independently before stroke. Participants will all receive standard local rehabilitation and will be randomly assigned either to receive regular feedback about activity levels, relative to a daily goal tailored by the smart watch over five time periods throughout a working day, or to no feedback, but still wearing the Smart watch. The intervention will last up to 3 weeks, ending sooner if discharged. The data to be collected in all participants include measures of daily activity (Smart watch measure); mobility (Rivermead Mobility Index and 10-metre walking time); independence in personal care (Barthel Activities of Daily Living (ADL) Index); overall activities (the World Health Organization (WHO) Disability Assessment Scale, 12-item version); and quality of life (the Euro-Qol 5L5D). Data will be collected by assessors blinded to allocation of the intervention at baseline, 3 weeks or at discharge (whichever is the sooner); and a reduced data set will be collected at 12 weeks by telephone interview. The primary outcome will be change in daily accelerometer activity scores. Secondary outcomes are compliance and adherence to wearing the watch, and changes in mobility, independence in personal care activities, and health-related quality of life.

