## Background

After stroke, practicing an activity and being active helps increase the speed and/or extent of recovery [1] but it is well-established that most inpatients in stroke rehabilitation settings have low levels of activity [2–4]. Increasing patients’ self-generated activity is possible through reorganizing care [5, 6] and could potentially play an important role in increasing independence.

Another way to increase activity and therefore to improve recovery of independence is to provide tailored feedback on activity and on progress towards goals. This could increase motivation, self-efficacy, and self-generated activity. Accelerometers can be used to record activity [2], and they can also be used to provide feedback; use of daily data by therapists can increase time spent walking [7]. There are several studies investigating the effect of feedback about physical activity from accelerometers to individuals. Some show no effect [8, 9] but some show beneficial effects [7, 10]. Benefits seem more likely if feedback is supported by other motivational support [11]. Most of these studies were published after the design of this project; there are many other study protocols published but not yet completed.

The primary objective of this study is to determine whether patient feedback about the amount of activity undertaken compared to their activity the previous day, provided at fixed time points during the day, will increase patient activity. We hypothesise that, compared to a control group who do not receive feedback from a Smart watch, those who receive feedback on daily activity will have increased physical activity levels, as measured by the activity scores, with no harms. We also hypothesize that this increased activity during inpatient stroke rehabilitation will result in improved mobility, and possibly cognition, arm function, independence in daily activities, and health-related quality of life. A third objective is to investigate the feasibility of setting up large-scale trials in a research-naïve setting. This protocol follows an initial pilot and feasibility study. ([name], [name], [name], [name], [name], [name], [name], [name], [name], [name], [name], [name], [name]: Augmented Feedback of Daily Activity on Physical Activity Levels after Acute Stroke: a pilot randomised controlled feasibility study, in preparation).

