Participants will be randomly assigned to one of two groups: (1) feedback of activity levels; or (2) no feedback of activity levels (i.e. control group). A block stratified randomization approach with two strata will be used, based on walking speed at the time of recruitment. A threshold of 0.42 m/s [12] will be used to define two groups: slow walkers (< 0.42 m/s) unlikely to walk in the community, and moderate-fast walkers (> 0.42 m/s). People unable to walk at the time of recruitment will be classified as slow walkers. The block size will be 5.

Once recruited, the recruiting doctor will inform the research office personnel, who are not blinded, and they will then undertake allocation. Allocation will be performed using a computer program in Microsoft Excel to allocate groups and generate numbers for each stratum (slow walkers or not slow walkers); the allocation will be made by the research office staff after registration. The research office will then notify the ward about the patient’s allocation by telephone. The researchers who will be performing all assessments will remain blinded to group assignment throughout the study.

The participants’ rehabilitation programmes will continue as normal, with no change in relation to this study. Therapists will not specifically be informed about a participant’s group, but may learn this. However therapists will not specifically encourage use of the feedback (or the opposite).

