**Fig. 4 Fig4:**
[figure not shown]
Standard protocol items: recommendation for interventional trials (SPIRIT) figure of study timing and activities. ADL, activities of daily living; WHO, World Health Organization

The first day will serve as a baseline measure, in which none of the participants will receive feedback on their activity levels. Thereafter each morning, an investigator will provide the participant with a Smart watch to be worn on the unaffected side and will remind the participant about the purpose of the watch; either to record activity (control group) or to provide feedback on activity (intervention group). Each evening an investigator will see the person, check that there have been no unexpected events or problems such as falls, or other adverse events, and then take the watch away so that data can be downloaded, and the watch recharged for use the next day.

In order to ensure that all researchers administer the intervention in a consistent manner, we will host a series of in-service training sessions on the use of the Smart watch. These in-services will focus specifically on the setup, data storage, and output from the CHMON system.

The control group will wear the same watch, and be seen each day by the researcher to collect the watch. In this way we will control for additional attention, and to an extent for any expectations generated by involvement in a trial and wearing a watch.

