Data will be collected by investigators trained in the use of the measures, using Chinese versions of the measures where relevant. The investigator will not know which group the participant is in. The following clinical data will be collected at baseline, end of intervention or at 3 weeks, and some will be collected by phone at 3 months (see Fig. 4):The Barthel Activities of Daily Living (ADL) Index (BI) [18], a 10-item scale that assesses the ability of an individual with a neuromuscular or musculoskeletal disorder to care for him/herself.The Rivermead Mobility Index (RMI) [19], a 15-item rating scale (14-self-reported items and 1 direct observation item) that assesses functional mobility following stroke (e.g. gait, balance, and transfers).The Montreal Cognitive Assessment (MOCA) [20] (Mandarin version) [21, 22], a 16-item scale that assesses the cognitive abilities designed to detect mild cognitive dysfunction.The Fatigue Severity Scale (FSS) [23–25], a 9-item scale that measures the severity of fatigue and its effect on a person’s activities and lifestyle.The World Health Organization 12 item Disability Assessment Schedule (WHODAS) [26], a questionnaire that assesses six domains of day-to-day functioning and provides an overall disability score based on this.The Euro-QOL (EQ-5D-3L) [27, 28], a questionnaire that provides a simple measure of health for clinical and economic appraisal. This questionnaire measures the dimension of mobility, self-care, usual activities, pain/discomfort and anxiety/depression.Grip strength [29] provides a quantitative and objective measure of isometric muscular strength of the hand and forearm.The 10-m walk test (10MWT) [30] assesses walking speed over 10 m.Spatio-temporal gait features at self-selected walking speed measured during a 10MWT using an inertial sensor (LPMS-B, Life Performance Research, Japan) on the lower trunk. Participants will be instructed to walk twice along a 10-m walkway at their normal pace with a walking aid or the support of a researcher. Walking speed, cadence, step length and symmetry of spatio-temporal measures will be calculated [31].

The outcome measure on which the intervention study is powered is change in activity scores as measured by a tri-axial accelerometer from a Smart watch.

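### The no-bias claim for the unaffected-wrist score does not hold between groups, because the same score is the feedback target in one arm only

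*Protocol article*

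**What the plan says.** All points are in the protocol article.

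- **Outcome.** The Abstract states: "The primary outcome will be change in daily accelerometer activity scores".
- **Interpretation.** The Background hypothesises that "those who receive feedback on daily activity will have increased physical activity levels, as measured by the activity scores, with no harms".
- **Sensor.** Each participant is to be given one watch, "provide the participant with a Smart watch to be worn on the unaffected side" (text after Fig. 4).
- **Double use.** The section on the CHMON feedback system says of the epoch scores that "these data are used, in the feedback group only, both to provide feedback to and to set goals for the patient". Each period's goal is 5% above the score for the same period on the previous day, and a bar display shows progress to it. Controls see only a clock.
- **Blinding.** The Design section says that participants cannot be blinded. Each morning they are reminded whether their watch is there to record or to give feedback.
- **The claim.** The CHMON section says that relative levels will be compared from day to day, over the treatment period and between groups. It then says that the "wrist of the unaffected arm, and a sampling procedure covering 20% of the time should allow this without risking systematic bias". In support it cites a correlation between a slightly modified score and energy expenditure.

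**The concern.** A measure can be imperfect and still give a fair comparison if its error is the same in both arms. Here allocation itself can change the error. Feedback patients know what the watch rewards and can satisfy it with the arm that wears it, for instance while seated. Controls have no such incentive. The relation between wrist score and whole-body activity may then differ by arm, and a difference of that kind is systematic bias in the between-group comparison.

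What is at stake is the meaning of a positive primary result. The Background would read it as more physical activity, with mobility expected to benefit. The data would support only the statement that feedback raised the quantity being fed back. The protocol does not warn of this; it says that the risk is absent.

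**Working it through.** **1. Which part of the claim fails.** The claim rests on sampling and on wrist placement.

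- Sampling: 30 s on and 120 s off gives 30/(30 + 120) = 20%, as stated. That is 9 × 3600/150 = 216 epochs per 9-hour day. The regime is the same in both arms, so it mainly adds noise.
- Placement: the sensor records one wrist, and its reading is displayed and rewarded in one arm only. The fault lies here.

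**2. Does comparing relative levels remove the problem?** It removes error that is constant within a person or equal across arms. It does not remove error that starts with the intervention and affects one arm. The first day, when nobody receives feedback, cannot correct for behaviour that begins when feedback begins.

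**3. How little arm movement would meet a goal (illustration).** Assume that a share *a* of the daily score comes from arm-only movement and that only this part rises, by *g*. The score then rises by *a* × *g*, so the 5% goal needs *g* = 5%/*a*:

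| Assumed share *a* | Rise in arm-only movement that meets the goal |
|---|---|
| 0.25 | 20% |
| 0.50 | 10% |
| 0.75 | 6.7% |

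**4. The effect the trial is powered for.** The inputs from Data handling and analysis are effect size 0.12, alpha 0.05, power 0.95, three measurement points and N = 182. The protocol does not name the effect-size metric or the correlation. I assume Cohen's f for the group-by-time interaction, correlation 0.5 and sphericity.

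- λ = f² × N × m/(1 − ρ) = 0.0144 × 182 × 3/0.5 = 15.72, with 2 and 2 × (182 − 2) = 360 degrees of freedom. Power is 0.952, and 182 is the smallest even N that reaches 0.95. The stated figure is reproduced.
- Other readings do not reproduce it: ρ = 0.3 gives 252, ρ = 0.7 gives 110, a between-group main effect gives 604 (ρ = 0.5), and two means with d = 0.12 gives 3610.

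To express f = 0.12 as a between-group difference in baseline-to-end change D (in SD units; at ρ = 0.5 the SD of change equals the SD of a single measurement):

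- Linear divergence: f = (D/4) × √(2/3), so D = 0.12/0.2041 = 0.59.
- Step, with the full difference from the second measurement on: f = D × √(1/18), so D = 0.12/0.2357 = 0.51.

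**5. An assumed artefact against that effect.** Assume an artefact equal to one 5% goal increment and an SD of change of 20% to 40%. Neither figure is in the protocol. The artefact is then 5/40 = 0.125 SD to 5/20 = 0.25 SD.

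| Artefact | Pattern | Share of powered D | Spurious f | Chance of significance, N = 182 | N = 160 |
|---|---|---|---|---|---|
| 0.125 SD | linear | 21% | 0.026 | 11% | 10% |
| 0.125 SD | step | 25% | 0.029 | 13% | 12% |
| 0.25 SD | linear | 43% | 0.051 | 30% | 27% |
| 0.25 SD | step | 49% | 0.059 | 39% | 35% |

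The last two columns assume no true effect, so the nominal value is 5%. N = 160 is the final recruitment given under Trial status.

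**6. Is the risk disclosed elsewhere?** The Discussion covers wear time, storage, the goal increment, duration, and the assumed link from general activity to mobility. It mentions neither wrist placement nor the use of one score as both target and outcome.

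**The case against.** The strongest reply is that the protocol defines its own construct. The Design section equates physical activity with movement, the Background ties the hypothesis to the activity score, and the CHMON section disclaims measuring actual activity. On those terms deliberate arm movement is activity. A wrist sensor also picks up walking and whole-body movement, and the cited correlation with energy expenditure gives the score some validity. Blinded assessors test mobility separately, so a score gain without a mobility gain would be visible. The clause is also hedged with the word should.

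Much of this stands. The score is a fair measure of whether feedback raises the watch score, and a positive result may be real. It does not rescue the no-bias clause. The disclaimer sits badly with a title and hypothesis about physical activity levels. The protocol does not say that the correlation was tested in stroke patients, on the unaffected arm, or in people rewarded for raising the score. The mobility measures assess function rather than amount of activity.

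A reader might go further in three ways that the document does not support:

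- **That a quarter of an SD would reproduce the whole powered effect**, by taking d = 2f = 0.24. That conversion does not fit the interaction that reproduces N = 182, for which the powered difference is 0.51 to 0.59 SD.
- **That regaining walking could lower the score**, because the good hand would hold an aid. Patients who cannot walk are enrolled ("People unable to walk at the time of recruitment will be classified as slow walkers"), but aids are mentioned only for the gait test ("walk twice along a 10-m walkway at their normal pace with a walking aid or the support of a researcher"). Nothing says which hand holds one or how the score responds.
- **That a claim of more activity should require a favourable Rivermead difference.** Activity could rise without a mobility gain within three weeks, and the Discussion itself says that a much larger study may be needed to show benefit.

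**Conclusion.** The concern holds in a limited form. The statement that the unaffected-wrist score supports between-group comparison with no risk of systematic bias is not justified, because unblinded patients in one arm only are shown and rewarded for that score. The fault is the placement combined with feedback on the outcome; the 20% sampling and the sample-size arithmetic are not at issue.

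The document establishes a risk and gives no basis for its size. The 21% to 49% of the powered effect is an illustration. It rests on an assumed 5% artefact, an assumed SD of change of 20% to 40%, and the reading of 0.12 as an interaction f with correlation 0.5. It should not be read as an estimate of bias, nor as evidence that a positive result would be false. What changes is what the primary result can be said to show.

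**What to change.** 1. In the CHMON section, delete the clause that denies a risk of systematic bias.
2. Describe the primary outcome as movement of the unaffected wrist during watch hours, and limit the primary conclusion to that.
3. Add to the limitations that the outcome is also the feedback target, in one arm only.
4. Report the primary effect within each walking-speed stratum, beside the blinded Rivermead, 10-metre walk and gait results. Treat these as supporting evidence, not as a condition the primary result must pass. The 10-metre walk and gait measures are collected but are not in the list of between-group comparisons under Data handling and analysis, so they need adding there.
5. If the slope of mobility change on score change is compared between arms, label it exploratory. Both variables are measured after randomisation, and a flatter slope in the feedback arm could not separate arm-only movement from real activity that has not yet improved mobility.

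All of this is wording and analysis of data already collected, so it remains possible although recruitment and follow-up have ended. The downside is a narrower headline claim from the primary outcome.
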